#### Individual randomized study

A sample of 440 HIV-positive men identified though mobile HTS at baseline will be randomized to either standard-of-care referral to ART or POC CD4 testing combined with personalized linkage to care. Randomization sequence will be generated in advance by the statistical center, using the Mersenne-Twister random number generator with seed derived from current system time. Randomization assignments will be placed into sealed tamper-proof numbered envelopes according to the generated sequence and released to study counselors in small batches. The envelopes will be used in the assigned order to reveal randomization results for individual participants. Lost or misplaced envelopes will be registered and tracked. The randomization sequence will be fully non-predictable.

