#### Cluster-randomized study

Eight communities of approximately 5000 persons (four intervention and four control communities) from the GEA and Vulindlela regions will be selected with an equal mix of rural and peri-urban communities to ensure greater generalizability of the intervention in different settings. Each of the communities will be randomized to either men-centered mobilization and testing strategies plus a small incentive or the control condition. Randomization will be performed by the statistical center in a restricted way, so that four communities are assigned to each arm. Randomization code will be written in R and will use the Mersenne-Twister random number generator with seed derived from current system time.

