#### Male-focused and delivered mobile HTS (Component 2)

The mobile HIV-testing services teams coordinate with CBM teams to ensure that testing happens according to the testing schedule. Copies of the testing schedule are distributed to community working groups, community-based outreach volunteers, local police stations, local health centers, and other community centers deemed appropriate by the study team.

Two HTS teams (four male nurse counselors and one driver per team) deliver easy-to-access mobile HIV testing through two mobile caravans. A mobile HTS team circulates through a range of male-centered locations in the community on a regular schedule of days and times suitable for men. Two teams serve the four intervention communities, with each team being responsible for two intervention communities over the course of the intervention. The team is supervised by a Counselor Supervisor.

CBMs are stationed in the vicinity of the men-centered spaces and engage men individually and in groups about the study. Mobilizers also inform men that a small incentive of R50 cell phone airtime (approximately US$5) would be received at completion of testing, regardless of HIV status. Other men in the vicinity of the mobile facility, but not necessarily frequenting the venues, are also encouraged to test by study staff. Recruited men are handed over to the study counselor at the mobile caravan for a fuller explanation of the study, informed consent, and completion of the HTS process.

Participants give consent for on-site POC procedures for screening for HIV and non-communicable diseases (NCDs) using rapid and POC tests. No specimens are retained for HIV and NCDs testing. In the event of a discordant HIV test result, a Dry Blood Spot (DBS) specimen will be collected from the participant for a laboratory confirmatory test to confirm serostatus. No specimens are retained for confirmatory tests. Participants who are eligible for enrolment (HIV-positive and not on antiretroviral treatment) and who consent to enrolment provide a DBS for baseline VL measures. Consent is provided for participants to be re-contacted at three and six months for study contact visits and for an exit visit at nine months after enrolment where participant exit survey data and end-line VL will be collected. Participants consent for their data to be stored and for secondary use of their data if such use is approved by the REC.

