#### HIV testing

HIV testing is conducted using blood collected by finger-stick with a sterile lancet and using a serial testing algorithm for rapid testing according to 2015 South African National HIV Test Services guidelines [75]. All specimens are first tested with one assay (Test 1 or screening test) and specimens that are non-reactive are considered HIV-negative and reported as such. Any specimens that are reactive on the first assay (Test 1) are tested again using a different assay (Test 2 or confirmatory test). For specimens that are reactive on both the first and the second assays, results are reported as HIV-positive. Specimens that are reactive on the first assay but non-reactive on the second assay will receive an ELISA laboratory test and be recorded as discordant. In the case of discordant results, the individual is given the schedule of mobile HTS testing locations and asked to return in seven days [7] for their HIV results.

Participants are triaged according to their HIV test result. HIV-negative participants will have completed their visit, as they are not eligible for further study participation and, if required, referrals to relevant services are made. Study counselors will explain to HIV-positive men in the intervention communities that they are eligible for the randomization and the next phase of the study, if interested. All HIV-positive participants are asked for locator information (addresses and alternate/additional contact phone numbers) so if randomized into the PLC arm they can be contacted. Permission is obtained to call and/or text the participant to arrange and keep in contact for PLC.

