#### Extended clinic hours for men (happy hour)

The PLC team leader negotiates with health services to ensure that extended hours of operation for obtaining ART and services are made available to PLC participants who have conflicting engagements during regular HIV clinic hours. This service (called happy hour) is already provided to young people by the Department of Health. A sample of clinics are opened once a week during 17:00 to 20:00, especially to cater for men. This male-only HIV service allows the PLC participants to feel more comfortable in accessing services and discussing their questions and concerns more freely with the staff at the after-hours HIV clinic. The after-hours HIV clinic will offer all services normally available at a standard HIC clinic during regular work hours including HIV testing, counseling, and ART medicines.

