#### Aim 2: Individually Randomized component

We will test the hypothesis that the proportion of HIV-positive men who were linked to care and maintained with undetectable VL nine months after enrolment will be the same in the POC + PLC arm as in the standard-of-care arm. The analysis will be based on men who were randomized and who completed the follow-up visit. We will use asymptotic tests for log odds ratios performed at the two-sided level of 0.05. Confidence intervals will be obtained by the same method.

#### Power calculations for Aim 2

Assuming that the rates of linkage to care and undetectable VL are 33% in the standard arm and 50% in the POC + PLC arm (odds ratio 2.0), the sample size of 175 individuals per arm yields 88% power to detect the effect of POC + PLC over standard of care. Adjusting for 20% attrition yields the sample size of 220 per arm.

#### Secondary analyses for Aim 2

We will carefully investigate the effect on attrition on the primary analysis of Aim 2. We will compare the men who do and do not present for the final visit to assess potential bias in the analysis of the primary endpoint of Aim 2. We will evaluate the attrition effect by multiple imputation of missing data using baseline characteristics of the individuals. We will compare HIV-positive men identified in Aim 1 who do and do not enroll in the Aim 2 study.

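### Aim 2 enrols men from four communities but states an odds-ratio test with no community term: a valid test that gives up a little precision, recoverable by stratifying the analysis

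*Protocol article*

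**What the plan says.** All references are to the protocol article.

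- **Who enters Aim 2.** Under HIV testing: "Study counselors will explain to HIV-positive men in the intervention communities that they are eligible for the randomization". Under Component 2 (mobile HTS): "Two teams serve the four intervention communities, with each team being responsible for two intervention communities". Aim 2 therefore draws on four communities and two field teams.
- **How they are allocated.** Under Individual randomized study: "Randomization sequence will be generated in advance by the statistical center", with assignments "placed into sealed tamper-proof numbered envelopes according to the generated sequence and released to study counselors in small batches". No stratum or block is named. The text does not say that there is none.
- **How they are analysed.** Under Aim 2: Individually Randomized component: "We will use asymptotic tests for log odds ratios performed at the two-sided level of 0.05", with confidence intervals by the same method. No covariate is named.
- **Planned size.** 33% against 50% success (odds ratio 2.0), 175 completers per arm for 88% power, and 220 per arm after allowing for 20% attrition.
- **The only between-community variance in the article.** 0.007, given in the Aim 1 power calculation for annual testing rates.

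**The concern.** Community of enrolment is fixed before randomization and should be known for every man. If success (linked, retained, undetectable viral load) differs between communities, a comparison that pools all men counts those differences as random error. A chance imbalance of arms within communities then also moves the estimate in the trial actually run. The article's own theoretical rationale lists distance to services, travel cost and quality of care as influences on treatment compliance, and these could plausibly differ by community. At stake is some precision in the Aim 2 comparison, at almost no cost to recover.

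**Working it through.** **Inputs.** From the Aim 2 power text: p1 = 0.33, p2 = 0.50, n = 175 completers per arm, two-sided alpha 0.05. From the Aim 1 power text: variance 0.007, so SD = sqrt(0.007) = 0.084. *Assumptions:* four equal communities, a common odds ratio across them, evenly spaced community effects on the logit scale, and overall rates held at 33% and 50%. The SD refers to control-arm success between communities.

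**Step 1: reproduce the plan's figure.** For an unstratified log odds ratio test, SE = sqrt[1/(n p1 q1) + 1/(n p2 q2)] and power = Φ(ln OR / SE − 1.96).

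- 1/3 against 1/2 (OR exactly 2.0): ln OR = 0.6931, SE = 0.2204, power 88.2%.
- 0.33 against 0.50 (OR 2.03): ln OR = 0.7082, SE = 0.2207, power 89.4%.
- Attrition: 175/0.8 = 218.75, so 219, stated as 220.

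The stated 88% is matched with no community term. The 89.4% is the reference below, because it uses the stated rates.

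**Step 2: is the unstratified test valid?** In simulations of 350 completers with simple 1:1 allocation (40,000 runs each), its type I error was about 0.050 at SD 0, 0.048 at SD 0.084 and 0.051 at SD 0.15. Its power stayed at about 0.90 in all three. It holds its level, and the planned power is not overstated.

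**Step 3: power of the community-stratified test.** With 43.75 men per arm in each community, let v_k = 1/(43.75 p1k q1k) + 1/(43.75 p2k q2k). Information is the sum of 1/v_k, and power = Φ(b × sqrt(information) − 1.96), where b is the common log odds ratio within communities.

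Worked case, SD 0.084:

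- control rates 0.222, 0.288, 0.363, 0.446; PLC rates 0.373, 0.457, 0.543, 0.627
- v_k = 0.2299, 0.2036, 0.1909, 0.1902; information = 19.76; SE = 0.2250
- b = 0.7334 (OR 2.08); 0.7334/0.2250 = 3.26; power = Φ(1.30) = 90.3%

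| Assumed SD of success between communities | OR within community | Power, stratified | Gain over 89.4% (points) |
|---|---|---|---|
| 0 | 2.03 | 89.4% | 0 |
| 0.05 | 2.05 | 89.7% | 0.3 |
| 0.084 (borrowed from Aim 1) | 2.08 | 90.3% | 0.9 |
| 0.10 | 2.11 | 90.7% | 1.3 |
| 0.12 | 2.14 | 91.3% | 1.8 |
| 0.15 | 2.22 | 92.2% | 2.8 |

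**Step 4: simulated check.** A Cochran-Mantel-Haenszel test against the unstratified test gave power of 0.904 against 0.897 at SD 0.084 and 0.929 against 0.902 at SD 0.15. At SD 0 it gave 0.898 against 0.900, a negligible loss. A separate run at SD 0.05 gave 0.901 against 0.898. The simulated gain is thus about 0.2 points at SD 0.05, about 0.8 at SD 0.084 and about 3 at SD 0.15.

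**Step 5: chance imbalance.** With simple allocation and 350 completers, its contribution to the risk difference has an SD of about 2 × 0.084/sqrt(350) = 0.9 percentage points.

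**The case against.** The strongest objection is that this is read from silence. A journal article commonly leaves strata and covariates to the full protocol or SAP, and the stated test could come from a logistic model with community terms. That stands in part: the article does not say that allocation is unstratified or that the odds ratio is crude. Against it, the article does report restriction for the community randomization, and its power figure matches an unstratified calculation.

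The second objection is that nothing is wrong: the test holds its level, the power is right, and chance imbalance is ordinary sampling error already inside the confidence interval. This stands in full, and it makes the point one of efficiency only.

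The third is that the gain is about one power point on a borrowed variance, in a trial that had enrolled 249 men by 30 November 2018. The size is fairly put. Enrolment so far does not prevent the change, provided it is fixed before outcome data are analysed.

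A reader might infer more than the documents support:

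- **That the planned test is biased or the trial underpowered.** Men are randomized individually, and Step 2 shows neither a level nor a power problem.
- **That these four communities were chosen to differ.** The phrase "equal mix of rural and peri-urban communities" describes the eight selected communities. The only restriction stated for randomization is four per arm, so a mix among the four intervention communities is not guaranteed.
- **That each community uses different clinics.** No section says so, and standard-care men may attend the nearest clinic or any service they choose.
- **That the extended hours ("A sample of clinics are opened once a week during 17:00 to 20:00") are a baseline difference between communities.** They are arranged for PLC participants, so they belong to the intervention. If access to them varied by community, that would be variation in effect, which a common odds ratio does not remove.
- **That 0.007 measures variation in Aim 2 success.** It describes testing rates.

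**Conclusion.** The point holds as a minor refinement. Aim 2 draws on four communities, and the stated analysis names no community term. The unstratified test is valid and its 88% power is delivered, so the cost is a small loss of precision and not an error. The gain from stratifying is about 0.2 to 3 points of power for assumed SDs of 5 to 15 percentage points, and about 1 point at 8.4. These figures rest on four equal communities and a common odds ratio. Since the article gives no variance for this outcome, the range should be read as illustrative. Confidence that stratification is truly absent is low, because the full protocol and SAP are not shown.

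**What to change.** In the Aim 2 analysis text, make the primary test and confidence interval stratified by community of enrolment: either a Mantel-Haenszel odds ratio over the four intervention communities, or logistic regression with community indicators (three extra terms). Report the crude odds ratio beside it. Fix the choice before outcome data are analysed. This matters more than usual here because the Blinding section says that the study statistician is not blinded. Allocation, envelopes and sample size stay as they are.

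The cost is about one sentence, plus a change in what is estimated: the odds ratio becomes conditional on community and moves slightly away from the marginal one, for example from 2.03 to about 2.08 at an SD of 8.4 points. Reporting the crude odds ratio keeps the marginal effect visible. If communities do not differ, the loss is negligible. If the full protocol or SAP already stratifies by community, no change is needed.

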#### Blinding

Due to the nature of the interventions, neither community-randomized nor individual-randomized intervention assignments are blinded to everyone. However, the laboratory results are completely blinded. The study statistician cannot be blinded because the intervention assignments were created by him and is also part of a team that conducts an unblinded review of process outcomes such as enrolment and dropouts in the study. Nevertheless the data processing and analysis will be done in the same impartial way in both intervention groups.

### Research ethics approval and data safety monitoring

The Institutional Review Board of the University of California, Los Angeles (UCLA, 00003962) and the Research Ethics Committee of the Human Sciences Research Council in South Africa (HSRC, REC 3/18/02/15) have approved the study and oversee adherence to the study protocol over time. A six-member Data Safety and Monitoring Board (DSMB), consisting of local and international experts, will monitor the implementation of the trial. National, provincial, district, and municipal health authorities approved the study and its protocol and set the conditions of the standard care practice.

The DSMB will review the effectiveness and scientific validity of the study. The DSMB will provide their evaluation feedback to the principal investigators and study sponsor assessing interim analyses on enrolment progress, protocol fidelity, and participant safety. Concurrently, enrolment progress is reported each trimester directly to the study sponsor. Ongoing harms and adverse monitoring is overseen by the local institutional research ethics committee (REC). A Community Advisory Board (CAB) consisting of community stakeholders, representatives, and leaders has been constituted for this study. Quarterly meetings are held with a CAB consisting of 25 local stakeholders who serve as liaison between research staff and the community, advising on study policies and keeping the community informed of progress. CAB members and study personnel have been trained to identify and report incidents of social harm and adverse events that may occur in the community to the study project manager. Regular feedback meetings are conducted with health authorities. The study project manager is responsible for logging, assessing, and actioning any appropriate remedial steps (onward referral, staff re-training, community messaging, etc.), reporting to the local REC and maintaining a register of incidents, if any, for the DSMB. The study will engage with participants’ preferred clinics for a formal feedback and update meeting on post-trial care. The study team will engage with the department of health and local health facilities to create a database of options (community-based re-supply, active support groups, and accredited health system partners). The study team will share this information with participants and facilitate access to programs for which the participants may be eligible, with referral to active support groups and adherence clubs.

### Research activities and procedures

#### Male-focused community outreach and mobilization (Component 1)

The community outreach team engage traditional leaders and key governmental and local stakeholders to obtain permission to conduct the study in the communities. Information is provided about the study aims and objectives as well as the rationale for including men in the intervention. The team identifies formal (e.g. community halls and churches) and informal social venues (e.g. transport hubs and sporting events) in each of the study communities where men are mobilized to participate in the study. At both venues, four community-based mobilizers (CBMs) conduct activities such as dialogues, social games, and distribution of pamphlets and edutainment to encourage men to test and link to treatment (see Table 1). Through these social networks, early adopters are identified and encouraged to test. Some of the early adopters are invited to be community champions (CC). CCs work with study staff to identify other men in their networks who are invited to participate in the intervention. These formal spaces are used for mobilization activities but also as possible spaces where mobile HIV testing is conducted. In addition, men identified through these venues are given information about the mobile HTS schedule and venues.

**Table 1 Tab1:** Men-centered mobilization strategies

Social games and edutainment	Different games are organized monthly per intervention community. These games include street soccer, field soccer, fun run/walk, card games, etc. These also include screening of soccer games on a big screen in taverns if a community Wi-Fi hot spot is available. While men participate in these games, health messages are distributed and testing is provided through the mobile van.
Men’s dialogues	The team organizes dialogues as a safe space for men to discuss matters pertaining to their health. Men are encouraged to be open about issues concerning them. Video clips of topics such as “AIDS in our community, Living positive with HIV/AIDS, Phuza Wise, Help stop women abuse, Alcohol and you” developed by a local communications non-governmental organization called Soul City (*https://www.soulcity.org.za*) are played to prompt discussion about men and their health. HTS staff are available to provide testing before and after each dialogue.
Pamphlets	Large amounts of pamphlets with study information are printed and distributed in taxi rank, taverns and sheebens, busy intersections, places of worships, and many other social venues. Posters are also pasted at strategic venues where are men are frequenting. Some of these posters provide general HIV testing FAQs and others are provide testing van schedule.

*HTS* HIV testing services

In addition to recruiting men to testing through formal and informal venues, CBMs go from house to house in the study communities to talk to men about healthy living and the importance of screening for HIV and other diseases. These CBMs also visit busy road intersections and talk with people who are passing by and distribute study information using pamphlets and appointment cards. In both these instances, men are provided information regarding when testing is likely to happen in their communities.

#### Male-focused and delivered mobile HTS (Component 2)

The mobile HIV-testing services teams coordinate with CBM teams to ensure that testing happens according to the testing schedule. Copies of the testing schedule are distributed to community working groups, community-based outreach volunteers, local police stations, local health centers, and other community centers deemed appropriate by the study team.

Two HTS teams (four male nurse counselors and one driver per team) deliver easy-to-access mobile HIV testing through two mobile caravans. A mobile HTS team circulates through a range of male-centered locations in the community on a regular schedule of days and times suitable for men. Two teams serve the four intervention communities, with each team being responsible for two intervention communities over the course of the intervention. The team is supervised by a Counselor Supervisor.

CBMs are stationed in the vicinity of the men-centered spaces and engage men individually and in groups about the study. Mobilizers also inform men that a small incentive of R50 cell phone airtime (approximately US$5) would be received at completion of testing, regardless of HIV status. Other men in the vicinity of the mobile facility, but not necessarily frequenting the venues, are also encouraged to test by study staff. Recruited men are handed over to the study counselor at the mobile caravan for a fuller explanation of the study, informed consent, and completion of the HTS process.

Participants give consent for on-site POC procedures for screening for HIV and non-communicable diseases (NCDs) using rapid and POC tests. No specimens are retained for HIV and NCDs testing. In the event of a discordant HIV test result, a Dry Blood Spot (DBS) specimen will be collected from the participant for a laboratory confirmatory test to confirm serostatus. No specimens are retained for confirmatory tests. Participants who are eligible for enrolment (HIV-positive and not on antiretroviral treatment) and who consent to enrolment provide a DBS for baseline VL measures. Consent is provided for participants to be re-contacted at three and six months for study contact visits and for an exit visit at nine months after enrolment where participant exit survey data and end-line VL will be collected. Participants consent for their data to be stored and for secondary use of their data if such use is approved by the REC.

After consent is obtained, the study counselor completes the utilization form on the mobile phone. The form includes basic sociodemographic information and information about previous testing behavior as well as engagement in HIV treatment and prevention and related health activities. If the male is not willing to participate, he will still complete the utilization form to allow for comparison of participants with non-participants.

